### Criteria for discontinuing or modifying allocated interventions

If a participant considers the dispensed spectacle frames are unsuitable or uncomfortable, they can return to the researcher for frame adjustment or dispensing of more appropriate frames. In this scenario, the lens interventions will not be changed.

If a participant experiences aversion or discomfort with one of the interventions, they can stop wearing the PTLs but will be asked to record reasons in the symptom diary. Participants will have previously worn any new optical prescription for 1 month before entering the trial to ensure that there is no non-tolerance to the optical prescription (see Additional file 1).

The participant can remain in the trial, regardless of how much they wear their PTLs, as long as symptom diaries are completed. Written and verbal communication will be provided to participants explaining this when the spectacles are dispensed.

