### Outcomes

#### Primary outcome measures

VS is defined as a condition characterised by symptoms [2], and a previous RCT [5] found symptoms to be the key outcome measure that demonstrated a benefit from individually prescribed PTL [5]. The clinical protocol for the detection, investigation, and management of VS starts with symptoms [26, 33]. Therefore, it is essential for pragmatic research on this topic to concentrate on symptoms. The first primary outcome measure will be symptom assessment using symptom diaries for each intervention. These symptom diaries were used by Wilkins et al. in the original RCT of PTL [5] (see Additional file 5). For the symptom diary, data will be divided into days and hours during which PTLs were worn and symptoms experienced.

The specific measurement variable will be symptom scores representing the number of symptomatic days with pair A vs pair B. The analysis will be carried out at the end of the 3-month trial, as participants will complete diaries throughout the trial.

The second primary outcome measure will be a further assessment of symptoms, measured via symptom questionnaires administered at baseline (before interventions) and at the end of each wearing period (with each intervention). The symptom questionnaire (Figs. 2 and 3) presents participants with questions (A) to (F). At follow-up appointments, the questionnaire wording will be slightly different so that the initial questions assess changes in the originally reported prime symptom (see Additional file 10).

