Initially, all data will be checked by scatter plots of raw data. All data will be tested for normality using the Shapiro-Wilk test, and non-parametric data will be transformed to parametric where possible. Simple comparisons will use paired *t*-tests, or the Wilcoxon signed-rank test as appropriate. For more complex analyses, a Mixed-Effects Model for Repeated Measures (MMRM) will be carried out to account for the crossover design, including fixed effects (intervention type, period, and sequence) and random effects (participant variability).

A confirmatory check will be performed to test for order effects (e.g. whether participants who have the optimal tint after the sub-optimal tint have a statistically different outcome from those who have the sub-optimal tint after the optimal tint). If such an effect is found, key analyses will be repeated whilst controlling for the order effect. In addition, an analysis of the effects of the first tint alone will be compared across participants. The analysis will have low power and will be confirmatory, but it is independent of order effects.

Participants for whom there is a complete set of symptom diary data for at least 2 weeks of wear with both interventions will be analysed on an intention-to-treat basis (ITT) [44]. In the unlikely event that any participants are misallocated, then key analyses will also be run according to a per protocol approach. For the symptom questionnaire conducted before enrolment in the trial and for the academic behaviour surveys, data will only be analysed for participants for whom data are available for *both*interventions [44].

Sensitivity analysis will also be carried out to confirm the robustness of the data produced.

The secondary outcome survey measures will be converted to numeric values. Scores will be aggregated and averaged across surveys and then prepared for statistical analysis using the approaches described above. Tertiary outcome measures will be assessed separately as an exploratory analysis. Tertiary outcome measures will undergo reliability testing using the intraclass correlation coefficient, and analysis for order effects using repeated measures ANOVA, before comparing interventions using standard *t*-tests.

All statistical analyses will be conducted using R (version 4.3.1, R Core Team 2023).

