Another strength of this study is the potential impact on society. If an individual suffers from symptoms of visual distortion, headaches, and eyestrain when reading, there is likely to be a tendency to avoid reading which may impact their educational achievement. This RCT will address the core symptoms of VS and help identify whether PTL have an effect on symptoms and WRRT performance in sufferers of VS using the Intuitive System. Improving the understanding of symptoms and potential treatment in those who report the symptoms of VS can provide health care professionals such as optometrists (who will be the most likely to encounter such symptoms in routine eye examinations) to provide patients with advice and, if appropriate, treatment.

Limitations of the trial are as follows. First, there is a risk with a single-site trial within a specialist clinic that the results may not be directly applicable to a more general population. However, the trial will recruit school-age participants from a variety of schools. Additionally, VS is typically treated in specialist optometric clinics, so the choice to base the trial in such a clinic is pragmatic as it reflects typical clinical practice.

Second, due to the requirement for daily diaries and multiple visits, there is a risk of participant attrition. However, the lead researcher aims to develop a positive rapport with participants and send frequent reminders as explained above. The importance of daily diaries lies within the findings of the original 1994 trial [9], where the daily diary analysis produced findings in the original RCT that were statistically significant, justifying a similar approach in this study. The use of reminders by modern technologies (e.g. SMS, WhatsApp, emails) should improve compliance with diary completion compared with the original study.

The results of this RCT aim to strengthen the evidence base concerning the existence and, if appropriate, treatment of VS using the IS.

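### Remaining in the trial is tied to completing the symptom diary, so a diary lapse can, read literally, end collection of outcomes that do not need the diary

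*Protocol article*

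**What the plan says.** Under Criteria for discontinuing or modifying allocated interventions, the protocol article states: "The participant can remain in the trial, regardless of how much they wear their PTLs, as long as symptom diaries are completed". The next sentence adds: "Written and verbal communication will be provided to participants explaining this when the spectacles are dispensed". Neither sentence says how much of the diary must be filled in.

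The diary is one of two primary instruments. Under Primary outcome measures, the other is described as "symptom questionnaires administered at baseline (before interventions) and at the end of each wearing period (with each intervention"). The parent and teacher surveys (secondary) and the Wilkins Rate of Reading Test, WRRT (tertiary), are separate again.

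The analysis section sets its own diary threshold for the intention-to-treat analysis: "Participants for whom there is a complete set of symptom diary data for at least 2 weeks of wear with both interventions". It then gives a second availability rule: "For the symptom questionnaire conducted before enrolment in the trial and for the academic behaviour surveys, data will only be analysed" where both interventions have data. That rule carries no diary condition. The Discussion acknowledges that "due to the requirement for daily diaries and multiple visits, there is a risk of participant attrition".

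**The concern.** The condition for staying in the trial rests on the most burdensome instrument, a daily diary kept by children, yet the other outcomes are collected without it. If the sentence is applied as written, a lapse on the diary becomes missing data on the second primary outcome, the surveys and part of the reading test. A family told of the condition in writing could also conclude that the child is out once the diary stops, without any formal withdrawal.

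This loss would occur after randomisation and could depend on the tint. The same section expects some children to stop wearing a tint that causes discomfort and asks them to record the reasons in the diary, so those with the worst experience are asked for continued diary effort. If children doing badly on the sub-optimal tint lapse, the remaining pairs understate the difference. If children who gain little from the optimal tint lapse, the remaining pairs overstate it. The documents do not settle the direction. The Background reports that attrition in the 1994 trial was criticised as a possible source of overestimated benefit.

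**Working it through.** **1. Three statements on the diary, side by side**

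| Section | What it requires |
|---|---|
| Intervention description | Diary kept for the whole month of wear |
| Criteria for discontinuing or modifying | Diary completed, undefined, as the condition for remaining |
| Statistical methods | Two complete weeks of diary per tint |

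Take a child who wears the lenses, fills in every day and stops the diary on day 16 of period 1. The analysis threshold of 14 days is met for that tint. On a strict reading of the retention condition, the child does not reach period 2. The threshold applies to both tints, so it cannot then be met. If *completed* means only enough for analysis, the child stays. The article does not say which is meant.

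**2. What a lapse would cost on the literal reading** (WRRT timing as in the Intervention description, at each dispensing and at the final visit)

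| Lapse | Already collected | At risk |
|---|---|---|
| Period 1 | Baseline questionnaire, survey and WRRT; first-pair WRRT | Second-pair WRRT, head-to-head WRRT, period-2 questionnaire and survey, hence every paired questionnaire and survey comparison |
| Late period 2 | All of the above, plus period-1 questionnaire and survey and second-pair WRRT | Period-2 questionnaire and survey, head-to-head WRRT |

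No diary check before the end-of-period visit is described, so whether a period-1 lapser still gives the period-1 questionnaire is open.

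**3. The plan's own sample size**

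Inputs from Sample size: effect 0.5 within-participant SD, 90% power, two-sided alpha 0.05.

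- Printed formula: n = 2(1.2816 + 1.9600)² / 0.5² = 84.06, so 85.
- Noncentral t version: df = n − 2, noncentrality 0.5·√(n/2). Power is 0.8999 at n = 86 and 0.906 at n = 88. The smallest even total with at least 90% power is 88, which reproduces the stated figure.
- Allowance from 88 to 120: 1 − 88/120 = 26.7%.

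**4. Power for the questionnaire contrast by total loss** (same t-based formula)

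| Total loss from 120 | n | Power |
|---|---|---|
| 10% | 108 | 95.4% |
| 20% | 96 | 92.9% |
| 26.7% | 88 | 90.6% |
| 30% | 84 | 89.3% |
| 40% | 72 | 84.1% |
| 50% | 60 | 76.8% |

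**5. Illustration of the rule's share of the loss**

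Assumptions, because the documents give no rates: 10–20% withdraw outright; a further 10–30% of the rest lapse; every lapser leaves before giving paired data; every lapser would otherwise have attended.

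- Condition enforced: n = 120 × 0.90 × 0.90 = 97 down to 120 × 0.80 × 0.70 = 67; power 93.1% to 81.4%.
- Condition not enforced: n = 108 to 96; power 95.4% to 92.9%.
- With 15% withdrawal, 88 evaluable participants remain as long as the lapse share is no more than 1 − 88/102 = 13.7%.

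**The case against.** The strongest reply is that the sentence is permissive. Its subject is lens wear, and its purpose is to keep non-wearers in. No section says that a lapse triggers removal, how large a lapse counts, or that other data collection then stops. The adherence section describes only reminders and rebooking, with diary reminders most frequent in the first two weeks, which fits the two-week analysis threshold. Detailed procedures and outcome collection are referred to Additional files 2 and 3, which are not shown and may cover follow-up after a lapse. The Discussion already discloses the attrition risk.

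Much of this stands, and it rules out several stronger readings that a reader might infer:

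- *That the protocol withdraws diary lapsers.* It states a condition for remaining but no removal step, so the loss is an inference from the wording.
- *That lapsers lose the reading test altogether.* Baseline and first-dispensing WRRT come before any diary with the first pair, and a period-2 lapser already has WRRT with both pairs.
- *That the second primary outcome has no usable availability rule, because the rule names the questionnaire given before enrolment.* Only end-of-period questionnaires can have data for both interventions, so this is probably a drafting slip. It should be corrected, but it does not show that the questionnaire analysis depends on the diary.
- *That the trial would be underpowered.* That depends on assumed lapse rates, and total loss up to 26.7% is already provided for.

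What does not fall away is the published condition itself and the plan to tell families about it. A more generous rule in the analysis section cannot recover questionnaires that were never collected.

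**Conclusion.** The point holds as a badly fixed retention condition, and it should be changed. The wording makes staying in the trial depend on one instrument, leaves the standard undefined and is not reconciled with the two-week threshold for analysis. Followed literally, it removes a period-1 diary lapser before crossover and so from every paired comparison.

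The main consequence is avoidable, possibly tint-related loss on the second primary outcome. Its size and direction cannot be derived from the documents. Power is a lesser matter: it falls below the planned 90% only if total loss goes beyond roughly the 26.7% allowance, and the range of 81.4% to 93.1% with the condition enforced rests entirely on the assumed rates. The stated sample size of 88 evaluable and 120 recruited does not change.

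**What to change.** - **Criteria for discontinuing or modifying:** replace the condition with a statement that participants remain in the trial and are invited to every visit, including crossover, end-of-period questionnaire, surveys and WRRT, regardless of lens wear or diary completion. Retention then no longer depends on the undefined term.
- **Participant information:** change the written and verbal explanation given at dispensing to match.
- **Statistical methods:** attach the both-interventions availability rule to the end-of-period questionnaires, and state that their analysis does not depend on diary completeness. The two-week threshold then governs the diary outcome only.

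The cost is about one sentence in each place, plus the ethics approval and registry update that the article requires for amendments. Trial status says that recruitment has not begun, so no participant has yet been given the present condition. The downside is slightly less pressure to complete diaries, which the planned reminders already address.

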### Strategies to improve adherence to interventions

The lead researcher will take the following steps to minimise the likelihood of dropouts. Participants/carers will be reminded via SMS every 3 days to complete symptom diaries daily for 2 weeks. Following this, an SMS reminder will be sent out once a week. The lead researcher will also ensure that missed visits are rebooked at a convenient time for the participant. The lead researcher will encourage academic survey completion by sending out reminders via SMS and email (with consent) to parents and teachers at the end of 1 month of wear. The lead researcher aims to develop a positive rapport throughout the trial and explain the importance of adherence to the trial at the time of consent and subsequent interactions.

### Relevant concomitant care permitted or prohibited during the trial

Only one PTL intervention will be issued per month of wear and participants will be asked not to use any other coloured filters, coloured paper, or modifications to digital device display colour. Participants may carry on with their education and daily life, as PTL wear will not interfere with daily tasks, and PTL wear is instructed to be for reading tasks (but not necessarily only for reading tasks if participants wish to wear them for other tasks, such as television or computer games).

### Provisions for post-trial care

After the trial, participants will be offered the PTLs from the trial that are more beneficial and will be allowed to continue wearing these if they wish to. Participants will be encouraged to continue to receive regular optometric care as would be recommended had they not participated in the trial.

### Outcomes

#### Primary outcome measures

VS is defined as a condition characterised by symptoms [2], and a previous RCT [5] found symptoms to be the key outcome measure that demonstrated a benefit from individually prescribed PTL [5]. The clinical protocol for the detection, investigation, and management of VS starts with symptoms [26, 33]. Therefore, it is essential for pragmatic research on this topic to concentrate on symptoms. The first primary outcome measure will be symptom assessment using symptom diaries for each intervention. These symptom diaries were used by Wilkins et al. in the original RCT of PTL [5] (see Additional file 5). For the symptom diary, data will be divided into days and hours during which PTLs were worn and symptoms experienced.

The specific measurement variable will be symptom scores representing the number of symptomatic days with pair A vs pair B. The analysis will be carried out at the end of the 3-month trial, as participants will complete diaries throughout the trial.

The second primary outcome measure will be a further assessment of symptoms, measured via symptom questionnaires administered at baseline (before interventions) and at the end of each wearing period (with each intervention). The symptom questionnaire (Figs. 2 and 3) presents participants with questions (A) to (F). At follow-up appointments, the questionnaire wording will be slightly different so that the initial questions assess changes in the originally reported prime symptom (see Additional file 10).

**Fig. 2 Fig2:**
[figure not shown]
Symptom questionnaire

**Fig. 3 Fig3:**
[figure not shown]
Symptom questionnaire

The two primary outcomes reflect fundamentally different methods of assessing symptoms. The daily diaries offer near real-time estimates of symptoms each day, providing a “live” assessment. In contrast, the questionnaires used at the end of each wearing period give a more long-term recollection of symptoms during that time and upon viewing a standardised passage of text through the relevant intervention.

The purpose of question (A) (Fig. 2) is to discover the presenting symptoms—what the participant considers to be their main problems when reading. In (B) (Fig. 2), the participant grades the severity of this symptom from 1 to 9. At follow-ups, participants will be asked to grade the same symptom again using the same scale, and this will be used to investigate changes with the interventions, with question (C) (Fig. 2) serving the same purpose (to investigate changes with the interventions) and to detect if there is a possible increase in the time spent reading with the interventions. Those who suffer from VS may avoid reading due to the presence of symptoms. Since this is the participant’s description of their main problems, it is clearly of utmost relevance to the participant and is therefore a suitable choice for a pragmatic trial.

The second part of the secondary outcome measures is addressed in questions (D), (E), and (F) (Fig. 3). Questions (D) and (E) (Fig. 3) ask participants questions according to the Delphi study. The questions about trait symptoms rely on the participant’s recollection of symptoms: trait symptoms are stimulus-specific, and reflect some of the Delphi [2] questions which also ask about the different aspects of the stimulus.

Question (F) of the symptom questionnaire is a compilation of the symptom questions used in the IC overlay test and assesses state, rather than trait. The questions ask about task-specific questions. Since these are the questions that practitioners using the IS believe are indicative of VS [13], it is pragmatic to use these symptoms as a primary outcome measure. These sections of the questionnaire comprised 6 questions, arranged on a five-point scale for sections (D) and (E) and a ten-point scale for (F) (Fig. 3).

The specific measurement variable will be symptom scores on a 5- and 10-point quantitative scale, representing symptom severity, with pair A versus pair B. However, a pilot study of the ARUTIS questionnaire will be conducted before finalisation to ensure that all items are age-appropriate and relevant and to verify that the questionnaire does not impose an undue burden on trial participants.

#### Secondary outcome measures

Secondary outcome measures will assess academic activity and behaviour by analysing surveys completed by parents/guardians and teachers under the two different intervention conditions.

Children with poor reading skills often have a heightened sensitivity to their poor reading and can be embarrassed by their perceived failures to read well. This can sometimes result in disaffection with reading as a whole and may contribute to poor academic outcomes and challenging behaviour. Studies have shown that 24% to 52% of children with learning difficulties present with problems with their behaviour [34]. Reading is involved in most schoolwork, and it seems likely that if a student has symptoms of headache, eyestrain, and visual perceptual distortions when reading, then this would deter them from reading [35]. This would be increasingly problematic as the child progresses through school because there will be a decrease in font size [36] and spacing which is likely to be associated with increased symptoms of VS.

Children suffering from symptoms of VS may manifest these as changes in behaviour (e.g. to avoid reading) rather than vocalising the symptoms of VS. Therefore, we have included an academic behaviour survey (seen in Additional file 6), to be completed by parents/guardians and a teacher at the end of each month of wear.

The specific measurement variable will be scored on a 5-point quantitative scale, representing the severity of VS symptoms, which manifest academically and behaviourally in pair A versus pair B. The analysis will be carried out at the end of the 3-month trial, as participants will complete questionnaires at baseline (referring to the situation before interventions) and at the end of each wearing period (referring to the situation with each intervention). The method of aggregation will be to average scores, and analysis of the questionnaire, along with the results from the primary outcome measure, will reveal whether pair A or pair B created the greatest reduction in VS symptoms.

Academic survey results may be influenced by factors unrelated to VS. However, the surveys are to be completed both before and after the intervention. The post-intervention results will reflect if VS symptoms create any effect on academic performance, rather than being the sole reason for poor academic achievement.

